**Baseline**				
Informed consent	✓			
Demographic	✓			
Arthritis status	✓			
Comorbidity	✓			
**Clinical and functional assessment**				
Knee function^a^	✓	✓	✓	✓
Quality of life^a^	✓	✓	✓	✓
Depression and anxiety^a^	✓	✓	✓	✓
Pain experience^a^	✓	✓	✓	✓
Activity level^a^	✓	✓	✓	✓
Dietary behaviours	✓	✓	✓	✓
Global assessment^a^		✓	✓	✓
Satisfaction with treatment^a^		✓	✓	✓
**Healthcare Utilization and Productivity Costs**^a^	✓	✓	✓	✓
**Quality of Care**	✓			

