**Methods:**

A multi-centre prospective cohort study of community ambulant knee OA patients seeking treatment in the tertiary healthcare institutions in Singapore will be conducted. Patients with secondary arthritis, significant cognitive impairment, severe medical comorbidities or previous knee arthroplasty will be excluded. Primary clinical outcome measure is the Knee injury and OA Outcome Score-12 (KOOS-12). Baseline characteristics include sociodemographic status, arthritis status including symptom duration and radiographic severity, comorbidities and functional status through Charlson Comorbidities Index (CCI), Barthel Index (BI) and Parker Mobility Score (PMS). Psychosocial variables include social support, kinesiophobia, negative affect, self-efficacy, injustice, chronic illness shame and the built environment. Clinical outcomes include quality of life, physical performance, global assessment, satisfaction and physical activity levels. Productivity and healthcare utilization will be assessed by a modified OA Cost and Consequences Questionnaire (OCC-Q) and the Work Productivity and Activity Impairment Questionnaire (WPAI). Variables will be collected at baseline, 4, 12 months and yearly thereafter. Regression, mediation and structural equation modelling will be used for analysis.

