#### Clinical, productivity and healthcare utilization outcomes

Recommendations set out by the OA Research Society International (OARSI) for domains of interest pertaining to non-surgical management of OA were adopted (i.e., pain, physical function, activity level, global assessment, and quality of life, etc.) [34, 35] for the clinical outcomes. The primary outcome will be Knee OA and Outcomes Score-12 (KOOS-12) [36]. The KOOS score has previously been validated in Singapore [37]. Other domains include quality of life, global assessment and symptom satisfaction (Tables 2 and 3).

**Table 2 Tab2:** Overview of outcome measures

Baseline Characteristics	Psychosocial Variables		Clinical, Productivity and Healthcare Utilization Outcomes	
**Sociodemographic**	**Depression and Anxiety**	Patient Health Questionnaire-4	**Knee Function**	Knee OA and Outcome Score (KOOS)
**Arthritis status**	**Pain catastrophizing/ fear of movement**	Brief fear of movement	**Quality of Life**	EQ-5D
**Comorbidities and Functional Status**	**Pain experience**	Pain intensity and interference PEG Scale	**Physical Performance**	Gait Speed Time-up-and-Go (TUG) Sit-to-stand (STS) Stair climb
	**Social support**	Multidimensional Scale of Perceived Social Support	**Physical Activity Level**	Step count UCLA activity level
	**Built Environment**^a^	Built environment questionnaire	**Dietary behaviour**	Dietary Questionnaire
	**Chronic Illness Shame**^a^	Chronic Illness Shame Scale	**Global assessment**	Global Perceived Effect
	**Religion and Spirituality**^a^	Religion questionnaire	**Symptom Satisfaction**	Patient Acceptable Symptom Scale
	**Injustice experience**^b^	Injustice Experience Questionnaire	**Cost, Productivity and Healthcare Utilization**	OA Cost and Consequences Questionnaire (including indirect costs and productivity)
	**Self-efficacy**^b^	Arthritis Self-Efficacy Scale	**OA Care Quality**^a^	OA Quality Indicator (OA-QI)

^a^To be administered in phase 1 of study

^b^To be administered in phase 2 of study

**Table 3 Tab3:** Outcome measures

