**8. Global and satisfaction**	
** Global Assessment**	The Global Perceived Effect (GPE) scale assesses the patient’s perception of knee OA progression [46]. It is a single item measure with 7-point Likert scale
** Satisfaction with treatment**	Patient Acceptable Symptom Scale (PASS) consists of an item pertaining to the perceived satisfaction of knee function, with a binary yes/no response [47]
** Treatment failure**	Perceived treatment failure will be assessed by an item about the participant’s current condition relating to the failure of the current course of treatment, with a binary yes/no response

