#### Outcome measures timepoints

Upon baseline outcome measure taking, participants will be followed up at 4 months, 12 months, and annually after that. To reduce respondent fatigue and keep questionnaire burden to the minimum, psychosocial variables will be administered in two phases (Table 2) with a core set of outcome measures collected at all time points. In addition, certain psychosocial variables eg. built environment, that are not anticipated to change significantly over time will only be taken at baseline (Table 4).

**Table 4 Tab4:** Data collection at different time points

Measure	Baseline	4 month	12 month	24 month

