**Psychosocial**				
Fear of movement	✓	✓	✓	✓
Self-efficacy	✓	✓	✓	✓
Pain acceptance	✓	✓	✓	✓
Injustice experience	✓			
Social support	✓			
Chronic illness shame	✓			
Religion and spirituality	✓			
Built environment	✓			

^a^Core outcome measures

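### PASS, a yes/no rating of the current knee state flagged as core, has no baseline measurement, so reaching an acceptable state cannot be told from already being in one

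*Protocol article*

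**What the plan says.** - Table 3 (block 8, Global and satisfaction) describes PASS under the label *Satisfaction with treatment*. It says the measure "consists of an item pertaining to the perceived satisfaction of knee function, with a binary yes/no response".
- Table 2 lists the same instrument, "Patient Acceptable Symptom Scale", under *Symptom Satisfaction*. The outcomes section agrees: "Other domains include quality of life, global assessment and symptom satisfaction".
- Table 4 carries the row "Satisfaction with treatment^a" with ticks at 4, 12 and 24 months and none at baseline. Its footnote explains the superscript as "Core outcome measures".
- The section Outcome measures timepoints says that psychosocial questionnaires are split into phases "with a core set of outcome measures collected at all time points". The abstract counts entry as one of those points: "Variables will be collected at baseline, 4, 12 months and yearly thereafter".
- The statistical analysis section plans linear regression for knee function and, as secondary analysis, mixed models for how outcomes change over time.

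No section gives a reason for the empty baseline cell or provides another baseline PASS reading.

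**The concern.** Two core rows in Table 4 lack a baseline tick: Global Perceived Effect and PASS. For the first this is sensible, because the item rates how the knee has progressed and has no meaning at entry. PASS as described asks about the present state and can be answered on day one.

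The study looks for psychosocial factors that forecast outcome and might be modified. A factor that merely goes with being satisfied at entry will also go with being satisfied later, because states persist. With a baseline value the analyst can separate the two. Without it, a yes at 4 months may be a patient who improved or one who was content throughout, and a model of PASS over time has no starting state. An analysis plan can choose covariates later, but it cannot recover an item that was never asked.

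**Working it through.** **1. The plan's own figures.** The documents give no PASS rate and no calculation for PASS. The only computed figure is the sample size. Reading the effect size as Cohen's f² = 0.05, a two-sided 5% test of one coefficient among 10 predictors with power 0.95 gives N = 262 (power 0.9501), as stated. The attrition sum is 262 × 0.2 × 3 + 262 = 419.2, stated as 420. Neither figure depends on PASS.

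**2. The schedule, side by side.**

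| Measure | Flagged core | Baseline | 4, 12, 24 months | What it rates |
|---|---|---|---|---|
| Knee function (includes KOOS-12) | yes | yes | yes | state |
| Pain experience (PEG) | yes | yes | yes | state |
| Quality of life (EQ-5D) | yes | yes | yes | state |
| Global Perceived Effect | yes | no | yes | change |
| PASS | yes | no | yes | state |

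Of these core measures, PASS is the only state measure without a baseline value.

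**3. Can someone already satisfied enter?** Table 1 requires activity-related joint pain but sets no minimum severity. Recruitment draws on the day's orthopaedic and physiotherapy lists, with no restriction to new or untreated patients. Entry while in PASS is therefore possible. How common it would be is unknown.

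**4. Illustration of persistence (all rates assumed).** Let p be the proportion in PASS at entry, s the proportion of these still in PASS at follow-up, and i the proportion of the others who reach it. The share of follow-up positives who were already positive is

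p·s / [p·s + (1 − p)·i].

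With s = 0.75 and i = 0.40:
- p = 0.20: 0.150 / (0.150 + 0.320) = 0.150 / 0.470 = 32%
- p = 0.30: 0.225 / (0.225 + 0.280) = 0.225 / 0.505 = 45%
- p = 0.40: 0.300 / (0.300 + 0.240) = 0.300 / 0.540 = 56%

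With p from 0.10 to 0.50 and (s, i) of (0.6, 0.4), (0.7, 0.3) or (0.8, 0.2), the share runs from 0.06 / 0.42 = 14% to 0.40 / 0.50 = 80%. The assumptions set the answer.

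**5. Illustration of an association (all rates assumed).** Step 4 does not measure bias in an association, so take a factor with no effect on either transition (s = 0.7, i = 0.3 in both groups) but linked to the entry state: 20% in PASS with the factor, 40% without.
- With the factor: 0.2 × 0.7 + 0.8 × 0.3 = 0.38
- Without: 0.4 × 0.7 + 0.6 × 0.3 = 0.46
- Odds ratio: (0.38 / 0.62) / (0.46 / 0.54) = 0.72

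The whole of this odds ratio comes from the difference at entry. Adjusting for baseline PASS would bring it to 1. Adjusting for baseline KOOS-12, PEG and EQ-5D would remove an unknown part.

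**The case against.** - **Predicting a later state is a valid prognostic aim.** The primary aim speaks of clinical outcomes and is not confined to improvement. This stands. A reader might infer that PASS cannot serve as a prognostic outcome at all, and the documents do not support that.
- **Entry severity is measured in other ways.** KOOS-12, performance tests, PEG, EQ-5D, PHQ-4 and activity level are all taken at baseline. This stands in part: they can stand in for baseline PASS but do not equal it.
- **The cohort is symptomatic.** Participants have activity-related pain and seek tertiary care, and the discussion expects more debilitating disease than elsewhere. This makes PASS at entry less likely but does not rule it out.
- **The article does not say how PASS will be coded or modelled.** This also stands. A reader might infer that patients satisfied at entry will be counted as treatment successes. The article does not say so, and that detail may sit in an analysis plan that is not shown.
- **The gap may be deliberate.** The row is labelled as satisfaction with treatment, and Table 3 groups it with Global Perceived Effect and treatment failure. Since Global Perceived Effect is rightly absent at baseline, the sentence on timing may just be loose. That may explain the empty cell, but the item as defined concerns the knee and is answerable at entry. Respondent burden is a weak reason for leaving out one yes/no question when the non-core dietary and built-environment questionnaires are taken at baseline.

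**Conclusion.** The point holds as a limit on interpretation and an inconsistency in the schedule. PASS is a core, current-state item without a baseline value. The text says core measures are taken at every time point, and no reason is given for the exception. PASS can be predicted as a follow-up state. It cannot show who attained an acceptable state as opposed to keeping one, its associations cannot be adjusted for its own baseline, and it cannot enter a model of change from entry.

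The size is unknown. The 32% to 56% share (14% to 80% over a wider set of inputs) and the odds ratio of 0.72 rest wholly on assumed rates, and the latter also on no adjustment for other baseline measures. They show that the effect could matter, not that it does. The primary outcome, KOOS-12, has a baseline value, and the sample size is untouched. This is a cheap improvement to a non-primary outcome and does not threaten the main analysis.

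**What to change.** 1. Add the single PASS item to the baseline form and tick the cell in Table 4.
2. Analyse follow-up PASS adjusted for baseline PASS, and report attainment among participants not in PASS at entry.
3. For participants already enrolled without the item, adjust for baseline KOOS-12 and PEG, and interpret PASS as a follow-up state only.
4. Relabel the row in Tables 3 and 4 to match *Symptom Satisfaction* in Table 2.
5. Amend the sentence in Outcome measures timepoints so that it excepts Global Perceived Effect, which has no baseline meaning.

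The cost is one yes/no question and a form amendment. The downside is that baseline PASS stays missing for those already enrolled. Because the sample size section keeps recruitment open throughout the study period, anyone who joins after the change would have it.

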**Psychosocial**				
Fear of movement	✓	✓	✓	✓
Self-efficacy	✓	✓	✓	✓
Pain acceptance	✓	✓	✓	✓
Injustice experience	✓			
Social support	✓			
Chronic illness shame	✓			
Religion and spirituality	✓			
Built environment	✓			

^a^Core outcome measures

### Sample size calculation

Sample size was estimated using G*Power 3.1.9.2. With a small effect size of 0.05, 0.05 type I error, 0.95 power of study and 10 predictive factors to be included into the model, the study will need to recruit 262 subjects. The final estimated sample size will be 420 cases after considering 20% attrition rate at each time point [(262 × 0.2) × 3 + 262] up to 2 years. Recruitment will be continued through the entire period to maximize statistical power.

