### Study aims

The primary aim is to identify critical psychosocial factors that prognosticate short and long-term clinical outcomes, productivity, and healthcare utilization in patients with knee OA.

The secondary aims areTo explore the mediation and directional relationship between the psychosocial factors with clinical outcome, productivity, and healthcare utilization outcome to support the development of a conceptual frameworkTo explore discordance between self-reported measures (SRM), physical-performance measures (PPMs), objective clinical parameters e.g. radiographic severity in knee OA and the extent to which psychosocial factors predicts the extent of discordance

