#### Prognostic factors that influence the rehabilitation outcomes

Linear regression modelling will be used to investigate the factors that influence the knee function of the patients. Simple linear regression will be used to explore the variables which significantly predict the outcome, and stepwise variable selection method will be used to build the multivariable models. Multicollinearity and interaction terms of the final model will be checked, and heteroscedasticity. The model fit will be checked and assessed using Hosmer-Leme show goodness of fit test. In secondary analysis, mixed effect generalized linear models will be used to explore the changes in outcomes across time as well as the factors predicting the outcome of interest. Mediation analyses will also be conducted to explore the potential mediating psychosocial factors between predictors with clinical outcomes. Structural equation modelling (SEM) cross lagged analysis, an analytical strategy used to describe reciprocal relationships or directional influences, between variables over time, will be used to estimate the directional effects of various psychosocial factors at different time points. Statistical significance will be denoted as *p* < 0.05.

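### The stated 0.95 power holds for one coefficient in a fixed 10-predictor model, not for the planned screening and stepwise search for several factors

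*Protocol article*

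**What the plan says.** The protocol article, *Sample size calculation*, gives its inputs in one sentence: "With a small effect size of 0.05, 0.05 type I error", then "0.95 power of study and 10 predictive factors to be included into the model, the study will need to recruit 262 subjects". The software is G*Power 3.1.9.2. The section names neither the procedure (single coefficient or whole model) nor the effect-size metric. It then raises 262 to 420 for attrition.

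*Study aims* sets a plural target: "The primary aim is to identify critical psychosocial factors that prognosticate short and long-term clinical outcomes".

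*Prognostic factors that influence the rehabilitation outcomes* describes the main analysis as linear regression. Simple regressions come first, to explore which variables significantly predict the outcome; then "stepwise variable selection method will be used to build the multivariable models". Significance is p < 0.05. No single coefficient is singled out, and no joint test of all the factors is mentioned.

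**The concern.** The sentence ties three things to one number: "0.95 power of study", "10 predictive factors to be included into the model" and 262. A reader will take it that the design has 0.95 power for the study's task, which is to find out which of about ten factors matter. The calculation that gives 262 answers a narrower question: whether one given factor, tested in a model whose other members are already fixed, has a non-zero coefficient. The planned analysis does not fix the model. It decides membership from the same data, first one variable at a time and then stepwise.

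What is at stake is how a factor that drops out will be read. If 0.95 is thought to apply to the search, the absence of a factor from the final model looks like good evidence against it. The planned procedure does not support that reading.

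**Working it through.** **Inputs** (*Sample size calculation*): effect size 0.05, alpha 0.05, power 0.95, 10 predictors, N = 262. Assumptions: 0.05 is Cohen's f², and the t test is two-sided.

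**1. Reproducing 262.** For one coefficient in a fixed model with p predictors, the error df is N − p − 1 and the noncentrality is δ = √(f²·N).
- N = 262, p = 10: δ = √(0.05 × 262) = √13.1 = 3.619; df = 251; critical t = 1.969. Normal approximation: Φ(3.619 − 1.969) = Φ(1.650) ≈ 0.95. Exact noncentral t: 0.9501.
- N = 261: 0.9494. So 262 is the smallest N that reaches 0.95.
- Other readings do not give 262: one-sided needs 218, and taking 0.05 as R² (f² = 0.0526) needs about 249.

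**2. What the 10 contributes.** The same single-coefficient calculation gives 262 for 1, 3, 5, 10, 15 or 20 predictors, because p enters only through the error df. Partial f² = 0.05 means that the one factor explains 0.05/1.05 = 4.8% of the variance left by the other nine.

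**3. Ten factors jointly (benchmark only).** Noncentral F with df (10, 251), λ = 0.05 × 262 = 13.1, critical F = 1.869: power 0.668. Reaching 0.95 would take N = 497, or a joint f² of 0.0965 at N = 262.

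**4. Per factor with alpha/10.** Alpha = 0.005, critical t = 2.832: Φ(3.619 − 2.832) = Φ(0.787) ≈ 0.78 (exact 0.783).

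**5. All ten found.** If each of ten factors has partial f² = 0.05 and the tests are independent, 0.95¹⁰ = 0.60.

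**6. Screening followed by stepwise selection.** Assume that the simple regressions act as a gate at p < 0.05, that all ten factors are real with partial f² = 0.05, and that residual variance is 1.
- *Uncorrelated factors.* In a simple regression the other nine effects go into the error: 1 + 9 × 0.05 = 1.45. Marginal f² = 0.05/1.45 = 0.0345; δ = √(0.0345 × 262) = 3.01; power to pass the screen ≈ Φ(3.01 − 1.97) = 0.85. Simulation of the whole procedure gives about 0.84.
- *Pairwise correlation 0.5, five positive and five negative effects.* The variance inflation factor is 1.818, so β² = 0.05 × 1.818 = 0.0909. Each covariance with the outcome shrinks to β × (1 − 0.5), squared 0.0227. The ten factors explain 0.0909 × 10 × 0.5 = 0.4545, so total variance is 1.4545. Marginal R² = 0.0227/1.4545 = 0.0156, f² = 0.0159, δ = √(0.0159 × 262) = 2.04; power to pass the screen ≈ Φ(2.04 − 1.97) = 0.53, before the stepwise step removes more.
- Simulations of the full procedure in positively correlated, mixed-sign settings gave per-factor power of 0.37 to 0.62. The fixed model kept about 0.95 on the same data.
- Where positively correlated factors all act in the same direction, the screen costs essentially nothing. The loss is possible, not certain.

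**The case against.** The strongest case for the plan is that nothing has been miscalculated. The single-coefficient procedure also takes the number of predictors in the model as an input, so the sentence fits the calculation that produced 262. The aim concerns individual factors, and a per-coefficient calculation is closer to it than a whole-model test. All of this stands.

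A reader might go further and infer that 262 is wrong, that the true power is 0.67, or that 497 analysable participants are required. The documents do not support that. They state no joint test and plan none. The 0.67 also changes the meaning of 0.05 from one factor's partial effect to the combined effect of ten. If one factor alone has partial f² = 0.05, the joint f² is at least that, so 0.67 is a floor; at a joint f² of 0.075 it is 0.87, and at 0.10 it is 0.96.

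It can also be said that 420 are to be recruited, not 262. But 420 is the number before losses, and 262 is the analysable number to which the power claim is attached. Whether the attrition allowance is adequate is a separate matter. Extra participants at earlier visits raise every figure but do not make a fixed-model power apply to a selected model.

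Finally, the plan adopts no multiplicity adjustment, the abstract calls the aim exploratory, and nowhere does the article say that an unselected factor will be treated as excluded with 95% power. That is right. It is an inference the wording invites, and the alpha/10 and all-ten figures are there for scale. A condensed article may also leave the procedure name to the full protocol, so that omission is not the point. What remains is the mismatch between two things the article does state: the power and the analysis.

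**Conclusion.** The point holds in a limited form. The 262 is correct for one given coefficient with partial f² = 0.05, two-sided alpha 0.05 unadjusted, in a fixed 10-predictor model. The label "0.95 power of study" is broader than that. It is not the power to identify all the relevant factors, and it is not assured for the screening and stepwise procedure, where per-factor power at 262 can fall from 0.95 to about 0.84, or to 0.37–0.62 in less favourable settings.

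Those last figures assume ten real factors of the stated size, a screen that acts as a gate at p < 0.05, and the correlation patterns given; with same-direction correlated effects there is little or no loss. The identification of 262 assumes that 0.05 is f², the only reading tried that reproduces the number. This is a power claim that the planned analysis does not carry, not a shortfall in recruitment.

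**What to change.** In *Sample size calculation*, restate the claim along these lines:

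> 262 analysable participants give 0.95 power (two-sided alpha 0.05, unadjusted) to detect any one given factor with partial f² = 0.05 in a fixed model containing 10 predictors. This is not the power to identify all the factors; at alpha/10 per factor it is 0.78.

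In the prognostic-factor analysis section, make a fixed 10-predictor model the analysis that this figure supports, with every coefficient and its confidence interval reported whether significant or not. The ten predictors have to be named before the outcome data are examined. Keep univariable screening and stepwise selection as exploratory, with no power claim attached.

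Cost: a less favourable power statement and a small change to the analysis text, so more than a rewording of one sentence. No extra patients, visits or measurements.

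### The attrition allowance adds 20% of 262 three times instead of dividing by retention, so 420 recruits leave about 215, not 262, at 2 years

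*Protocol article*

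**What the plan says.** All of this is in the protocol article, section Sample size calculation. The calculation was done in G*Power: "With a small effect size of 0.05, 0.05 type I error, 0.95 power of study and 10 predictive factors to be included into the model", from which "the study will need to recruit 262 subjects". That figure is then raised to "420 cases after considering 20% attrition rate at each time point [(262 × 0.2) × 3 + 262] up to 2 years". The section closes with "Recruitment will be continued through the entire period to maximize statistical power" and gives no number above 420.

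The section Outcome measures timepoints and Table 4 put follow-up at 4, 12 and 24 months, which are the three time points in the formula. The primary outcome, KOOS-12, falls under knee function, which Table 4 schedules at baseline and at all three follow-ups. The primary aim covers both short-term and long-term outcomes.

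**The concern.** The 262 is the number that must be available for analysis. Attrition acts on the number recruited, which is larger. The plan applies the 20% to the 262 and adds the result three times, so it allows for fewer losses than its own rate implies. The number recruited should be the number needed divided by the proportion retained.

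The allowance runs to 2 years, so the 2-year analysis is the one it has to cover. If the allowance is too small, that analysis has fewer subjects and a higher chance of missing a real prognostic factor than the article states. Readers would take 0.95 power to apply to the long-term results when it does not.

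**Working it through.** **Inputs (Sample size calculation, unless noted)**
- Effect size 0.05, read as Cohen's f² for linear regression
- Type I error 0.05; the article does not say whether one- or two-sided
- Power 0.95; 10 predictors
- Number needed before attrition: 262
- Attrition: 20% at each time point
- Follow-ups to 2 years: three, at 4, 12 and 24 months (Outcome measures timepoints; Table 4)

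**Step 1: reproduce 262.** The article does not name the G*Power test. For a t-test of one regression coefficient, the degrees of freedom are N − 10 − 1 and the noncentrality is √(f² × N). At N = 262 this gives 251 degrees of freedom and noncentrality √(0.05 × 262) = 3.619. Two-sided power is 0.9501, against 0.9494 at N = 261, so the smallest N reaching 0.95 is 262, exactly the plan's figure. Other choices do not reproduce it: the one-sided version gives 218 and the overall test of all 10 predictors gives 497. The two-sided single-coefficient test is used below.

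**Step 2: reproduce 420.** 262 × 0.2 = 52.4; 52.4 × 3 = 157.2; 157.2 + 262 = 419.2, stated as 420.

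**Step 3: apply the stated attrition to 420.** Taking 20% of those still in follow-up at each wave:

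| Follow-up | Calculation | Expected number | Power at f² = 0.05 |
|---|---|---|---|
| 4 months | 420 × 0.8 | 336 | 0.983 |
| 12 months | 420 × 0.8² | 268.8 (about 269) | 0.955 |
| 24 months | 420 × 0.8³ | 215.0 | 0.904 |

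The 24-month shortfall is 262 − 215 = 47 subjects, or 47/262 = 18%. The type II error there is 1 − 0.904 = 9.6%, about twice the 5% stated. With N = 215, the f² detectable with 0.95 power is 0.061 rather than 0.05.

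**Step 4: the number consistent with the inputs.** 262/0.8³ = 262/0.512 = 511.7, so 512 recruits (513 if rounded up at each wave).

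**Step 5: the alternative reading.** If each 20% is of the original sample, retention at 24 months is 1 − 3 × 0.2 = 0.40. Then 420 × 0.40 = 168 remain, power is 0.821 (type II error about 18%), and 262/0.40 = 655 recruits would be needed. This reading also fails to give 420.

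**Step 6: what loss rate would make 420 right?** Keeping 262 of 420 through three waves requires a loss per wave of 1 − (262/420)^(1/3) = 14.6%, or 1 − 262/420 = 37.6% overall. The plan states 20% per wave, which is 1 − 0.512 = 48.8% overall.

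**The case against.** Several points can be made for the plan.

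- **Size.** On the compounding reading, 24-month power is about 0.90, which is respectable for an observational prognostic cohort, and the detectable f² moves only from 0.05 to 0.061. This stands. The study is not endangered, but the stated figure is still wrong.
- **No primary time point.** The statistical section does not single out 24 months for the linear regression, and the target is met at 4 and 12 months. This stands as a limit on the finding. However, the formula itself runs to 2 years, so the 0.95 is presented as holding there.
- **Open-ended recruitment.** 420 may act as a floor, and the number actually enrolled may be larger. That is possible, but no higher target is given, and extra enrolment would not make the calculation correct.
- **Imputation and mixed models.** Both are foreseen and may recover some information. The sample size section takes no credit for either, the mixed models are secondary, and imputing a missing outcome from baseline covariates restores little.
- **Non-cumulative absence.** If 20% were simply absent at each visit, 336 would be present at 24 months and 420 would be more than enough. But one such loss would need only 262/0.8 = 327.5, so 328 recruits. Adding three losses shows that the plan treats attrition as cumulative.
- **The harsher reading.** The figures 168, 0.82 and 655 imply 60% total loss and are the less natural reading. They are best kept as an outer bound; the main figures are 215, 0.90 and 512.

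**Conclusion.** The concern holds. On the plan's own inputs, 420 recruits give about 215 at 24 months, not 262, and power there is about 0.90 instead of 0.95. The number consistent with 0.95 power at 2 years is 512. At 4 and 12 months the claim is met.

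The error in the attrition formula does not depend on which test was used. The power figures do: they assume f² = 0.05, a two-sided 0.05 test of one coefficient among 10 predictors, analysis of those observed at the visit, exactly 420 recruited, and 20% of those remaining lost at each wave. If the 20% is of the original sample, 24-month power falls to about 0.82.

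**What to change.** In Sample size calculation, replace the additive formula with 262/0.8³ and say that each 20% is of those still in follow-up. Then choose one of two statements:

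1. Keep 420 and report what it delivers: about 269 at 12 months (power about 0.95) and about 215 at 24 months (power about 0.90, or 0.95 power for f² = 0.061).
2. Give 512 as the recruitment figure that preserves 0.95 power at 2 years.

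In either case, name the test behind 262 so that the power statements can be checked. If recruitment is to continue past 420, state the number it aims for.

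The first option costs two sentences and no extra patients; the stated 2-year power becomes slightly less favourable. The second needs 512 − 420 = 92 more recruits than the current target.
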